## **2. STUDY OBJECTIVES AND ENDPOINTS**

### **2.1 Objectives**

- To collect blood and urine samples in cisplatin-treated patients and control subjects.
- To characterise the within- and between-subject baseline variability of novel biomarkers relative to BUN/ serum creatinine in these populations.
- To compare the patterns of novel biomarker changes relative to BUN/ serum creatinine following cisplatin treatment. These data will be used to:
  - select candidate biomarkers to progress to the confirmatory stage of biomarker qualification and establish cut-off values for these biomarkers.
  - determine the optimum method of expressing (corrected vs. uncorrected) each novel urinary marker relative to urinary creatinine for subsequent studies.
  - characterise the time course of biomarker changes to optimise the study design and sample collection time-points of confirmatory studies.

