|                   | Clusterin                                         | Marker of tubular injury/regeneration (no apparent specific nephronal localization) |
|                   | Neutrophil gelatinase associated lipocalin (NGAL) | Marker of tubular (mainly proximal) injury                                          |
|                   | Trefoil Factor 3 (TFF3)                           | Marker of proximal tubular injury                                                   |
|                   | Osteopontin                                       | Marker of injury to distal regions of nephron                                       |
|                   | Tissue inhibitor of metalloproteinase-1 (TIMP-1)  | Marker of interstitial fibrosis and tubular injury                                  |
|                   | Connective Tissue Growth Factor (CTGF)            | Marker of interstitial fibrosis                                                     |
|                   | Interleukin-18 (IL-18)                            | Marker of inflammation                                                              |
|                   | Monocyte chemoattractant protein-1 (MCP-1)        | Marker of inflammation                                                              |

\* All biomarkers will be assessed in urine and Cystatin C and NGAL will additionally be assessed in plasma/serum.

A 10 mL EDTA blood sample will be taken at the baseline and Day 7 visits only. The plasma obtained from these samples will be stored for future use for novel renal and other organ safety biomarkers.

Additional the following parameters will be assessed in the 5 ml blood plus 10 ml urine for routine diagnostics.

|                 |                                                                                                        |
|-----------------|--------------------------------------------------------------------------------------------------------|
| Blood Chemistry | Total protein, Albumin, Creatinine, Urea
Sodium, Chloride, Calcium, Phosphate, Potassium, Magnesium |
| Urinalysis      | U-Kreat; U-Urea; Na, K, U-Protein, U-Albumin (Midstream)                                               |

**Table 4:** Type of Samples and Approximate Amount of Blood and Urine to be collected from Each Subject

| Test                      | Sample volume (mL) | Number of visits sampled |                | Total volume (mL) |                |

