### **9.2 Statistical Analysis**

#### **9.2.1 Analysis of Primary Endpoint**

The full list of novel serum and urinary biomarkers (BM) included in the analysis are provided in Table 3 (Section 7).

The statistical distribution of the baseline BM values will be described graphically and by calculating the mean, median, standard deviation, inter-quartile range and range within each cohort and overall. The form of the relationships between each pair of BMs will also be investigated.

For each BM, the profile of values over time will be summarised and inspected to see if any patterns of change differ between the cisplatin cohort and the two control cohorts. BMs that show a different response between cohorts will be further investigated to characterise the form of the response and to evaluate if the response appears associated with concurrent changes in serum creatinine and BUN.

BMs will be assessed, one at a time, for their ability to predict DIKI as defined by the AKIN and RIFLE criteria[refs]. In addition, each patient in the cisplatin cohort will be reviewed by an adjudication panel to assess presence of DIKI using all of the available data. BMs will also be assessed for their ability to predict DIKI as defined by the adjudication panel. Exploratory ROC curves will be generated and estimates of sensitivity and specificity will be given. BMs will be ranked according to their estimated probability of having a sensitivity and specificity of greater than 80% for predicting DIKI.

Exploratory analyses may also be conducted to evaluate the potential for combining BMs to enhance prediction of DIKI.

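### The adjudication panel may use the novel biomarkers to assign DIKI and the same biomarkers are then scored against its verdict, so panel-based accuracy may be inflated

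*Protocol*

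**What the plan says.** Section 9.2.1 gives two kinds of reference standard for DIKI. The first is rule-based: "BMs will be assessed, one at a time, for their ability to predict DIKI as defined by the AKIN and RIFLE criteria". The second is a panel, introduced as an addition: "each patient in the cisplatin cohort will be reviewed by an adjudication panel to assess presence of DIKI using all of the available data". The sentence after that reads "BMs will also be assessed for their ability to predict DIKI as defined by the adjudication panel".

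The same paragraph then states "Exploratory ROC curves will be generated and estimates of sensitivity and specificity will be given", and the markers are to be "ranked according to their estimated probability of having a sensitivity and specificity of greater than 80% for predicting DIKI". That last sentence does not say whether DIKI means AKIN, RIFLE or the panel. Section 2.1 gives the use of the results: to "select candidate biomarkers to progress to the confirmatory stage of biomarker qualification and establish cut-off values for these biomarkers". Section 9.2.2 also counts panel-defined DIKI within a secondary endpoint, the incidence of DIKI.

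The candidate markers are in the biomarker table of Section 7 (Table 3) and are sampled at every study visit from pre-dose onwards. The routine urinalysis in the same section comprises "U-Kreat; U-Urea; Na, K, U-Protein, U-Albumin (Midstream", so urinary albumin and urinary creatinine are in both lists. Section 9.4 plans an interim analysis of the biomarker endpoints once data from 30 cisplatin patients are available.

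**The concern.** A reference standard should be set without the test that it will judge. Here the panel's evidence is defined by an inclusive rule with no exception, and the novel markers are study data on every cisplatin patient. No section masks the panel, limits its data or requires its verdict before biomarker results are released. A panel that followed the text could use a marker to decide that a patient has DIKI, and the marker would then be credited with detecting it.

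Section 1.1 suggests where this would matter most. It says that BUN and creatinine may miss injury until at least half of renal function is lost, and usually change only after 3 to 5 days. Where those tests are unremarkable, an unmasked panel has the most reason to lean on the new markers.

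At stake are the panel-based ROC curves, sensitivities and specificities. If the ranking uses the panel definition, the choice of markers for the confirmatory stage and their cut-offs are at stake too.

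**Working it through.** **The plan's own figures.** The protocol states no panel-based sensitivity or specificity, so there is none to reproduce. Two figures bracket a plausible DIKI rate: at least 20 AKI cases in 100 cisplatin patients (Section 9.1, 20%) and nephrotoxicity in about one-third (Section 1.1).

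**Assumptions, none from the protocol.** DIKI rate π = 25% as judged by a masked panel. Against that panel the marker has sensitivity s = 70% and specificity c = 75%. When the marker and the masked verdict disagree, an unmasked panel adopts the marker's call in a share f of those patients.

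**Starting cells.**
- TP = πs = 0.25 × 0.70 = 0.1750
- FN = π(1 − s) = 0.25 × 0.30 = 0.0750
- FP = (1 − π)(1 − c) = 0.75 × 0.25 = 0.1875
- TN = (1 − π)c = 0.75 × 0.75 = 0.5625

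**After the panel adopts the marker's call in a share f.** TP′ = TP + f·FP; FN′ = (1 − f)·FN; FP′ = (1 − f)·FP; TN′ = TN + f·FN. Apparent sensitivity = TP′/(TP′ + FN′) and apparent specificity = TN′/(TN′ + FP′).

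| f | TP′ | FN′ | FP′ | TN′ | Sensitivity | Specificity |
|---|---|---|---|---|---|---|
| 0 | 0.17500 | 0.0750 | 0.18750 | 0.5625 | 70.0% | 75.0% |
| 0.1 | 0.19375 | 0.0675 | 0.16875 | 0.5700 | 74.2% | 77.2% |
| 0.2 | 0.21250 | 0.0600 | 0.15000 | 0.5775 | 78.0% | 79.4% |
| 0.3 | 0.23125 | 0.0525 | 0.13125 | 0.5850 | 81.5% | 81.7% |

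**Other DIKI rates, same marker, f = 0.3.** At 20%: 0.200/0.242 = 82.6% and 0.618/0.758 = 81.5%. At one-third: 0.2833/0.3533 = 80.2% and 0.5300/0.6467 = 82.0%. The DIKI rate matters much less than f.

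**Other markers, 20% DIKI rate (sensitivity/specificity).**

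| Against a masked panel | f = 0.1 | f = 0.2 | f = 0.3 |
|---|---|---|---|
| 50/50 (no information) | 60.9/53.2 | 69.2/56.8 | 75.9/60.6 |
| 70/70 | 75.2/72.4 | 79.7/74.9 | 83.5/77.5 |
| 75/75 | 79.1/77.1 | 82.6/79.2 | 85.7/81.5 |

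Both measures rise at every f above zero, but whether both exceed 80% depends on the marker and on f.

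**Direction against true injury.** In a simulation of 1,000,000 patients with 20% truly injured, standard evidence was normal with a shift of 2 SD in the injured. The panel score was (1 − w) × standard evidence + w × marker, and the top 20% were called DIKI. AUC against the panel:

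| Marker | True AUC | w = 0 | w = 0.1 | w = 0.2 | w = 0.3 | w = 0.5 |
|---|---|---|---|---|---|---|
| Pure noise | 0.50 | 0.500 | 0.535 | 0.579 | 0.634 | 0.782 |
| Shift 1.2 SD | 0.801 | 0.692 | 0.730 | 0.770 | 0.809 | 0.888 |

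Against a masked panel (w = 0), every positive weight inflates the AUC. Against truth, the useful marker is understated at w = 0.1 and 0.2 and overstated at 0.5, because a masked panel is itself imperfect.

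**The case against.** The strongest reply is that the protocol does not say that the panel will see the novel markers. What is available to the panel, and when, could be set in an adjudication charter or the SAP, neither of which is at hand. This stands against any claim that the bias will occur. It does not clear the text: the protocol does more than leave the evidence open, because it states an all-inclusive rule, and a charter that masked the panel would depart from it.

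The analyses are also labelled exploratory, the panel is the additional standard, and the AKIN and RIFLE results would remain as a check: a marker that did well only against the panel would look discordant. This limits the damage. It does not remove it, because the stated output is a selection of markers and cut-offs.

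The worked figures rest on assumed adoption rates and on a panel that defers to a single marker, although Table 3 of Section 7 lists more than 20. That is fair, and it is why a range is shown.

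Finally, a reader might infer from the 30% row that a marker failing an 80%/80% criterion would pass it. The protocol has no such criterion. It ranks markers by the estimated probability of exceeding 80% on both measures, so inflation would move a marker up a ranking; it would not carry it through a gate.

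**Conclusion.** The point holds as a defect of wording: Section 9.2.1 permits incorporation bias in the panel-based analyses. Relative to a masked panel, sensitivity, specificity and ROC estimates may be inflated. In the main example (25% DIKI, a 70%/75% marker) the gain is about 4 and 2 percentage points at 10% adoption, 8 and 4 at 20%, and 11 and 7 at 30%. The protocol gives no basis for choosing among these.

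Two stronger readings are not supported. One is that the panel-based estimates are inflated: the documents do not establish that the panel will see or use the markers, and against true injury the net error can go either way. The other is that the ranking and selection are distorted: they can be, because the ranking sentence leaves the DIKI definition open, but if it uses AKIN or RIFLE they are untouched.

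The wording should be settled before adjudication begins. Verdicts given with the markers in view could be repaired only by a fresh masked adjudication.

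**What to change.** In Section 9.2.1, replace the closing phrase of the adjudication sentence, which sets the panel's evidence, with: *using clinical data, concomitant medication, adverse events and routine laboratory data, masked to the results of all novel biomarkers in Section 7 (Table 3)*.

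Add three rules:

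- Each patient's panel verdict is locked before the panel has access to that patient's biomarker results.
- Panel members take no part in, and do not see, the interim biomarker analysis of Section 9.4.
- For urinary albumin and urinary creatinine, which are in both Table 3 and the routine urinalysis, either withhold the routine results from the panel, or flag their panel-based accuracy as not independent of the reference standard.

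No new data, samples or visits are needed. The costs are the sequencing of adjudication and a firewall between the panel and the interim analysis. If the routine urinary albumin and creatinine results are withheld, the panel also loses some evidence; flagging avoids that loss but leaves those two markers without an independent panel-based estimate.

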Cisplatin is a widely used and potent chemotherapy drug administered alone or in combination for the treatment of a number of cancers such as testicular, head and neck, ovarian, cervical and non-small cell lung carcinoma, amongst other [Pabla and Dong, 2008]. Its use is limited by adverse effects, notably nephrotoxicity. This occurs in about one-third of patient undergoing high dose cisplatin treatment. Clinically, nephrotoxicity is often seen within about 10 days of cisplatin administration and is manifested as lower glomerular filtration rate, higher serum creatinine, and reduced serum magnesium and potassium levels. It causes proximal and distal convoluted tubular damage by entering tubular cells and activating apoptotic pathways that result in cell death. It also induces the production of TNF, triggering a robust inflammatory response and further contributing to tubular cell injury and death. Cisplatin may also induce injury in the renal vasculature, leading to ischemic tubular cell death and decreased glomerular filtration rate (GFR). Together, these pathological events culminate in acute renal failure in a proportion of patients [Pabla and Dong, 2008].

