## **9. DATA ANALYSIS/STATISTICAL METHODS**

### **9.1 Sample Size**

The maximum sample size for this multiple cohort observational study is 140 patient/subjects comprising;

- 100 patients in the cisplatin cohort to have a minimum of 20 subjects who show post-cisplatin BUN and serum creatinine changes that qualify as AKI.
- 20 patients in the patient control cohort.
- 20 subjects in the volunteer control cohort.

A sample size of 100 patients in the cisplatin cohort and 20 patients/subjects in each control cohort will enable a reliable assessment of the form of the statistical distribution for baseline values for each novel BM. In addition, a sample size of 20 cisplatin patients with AKI and 20 patients/subjects in each control cohort will enable an exploratory comparison between cohorts to detect patterns of difference in the BM profiles over time.

The sample size of the cisplatin-treated and the control cohorts may be adjusted during the course of the study based on interim analyses of novel biomarker patterns as well as the incidence of AKI as defined by BUN and serum creatinine changes in the cisplatin cohort.

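### Section 9.2.1 estimates marker accuracy in the same patients used to set cut-offs and choose the expression, so the figures for the leading markers will be optimistic, mainly in sensitivity

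*Protocol*

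**What the plan says.** Protocol 2.1 gives the data from this study several jobs. One is to "select candidate biomarkers to progress to the confirmatory stage of biomarker qualification and establish cut-off values for these biomarkers". Another is to "determine the optimum method of expressing (corrected vs. uncorrected) each novel urinary marker relative to urinary creatinine for subsequent studies".

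Protocol 9.2.1, under the primary endpoint, assesses markers one at a time for predicting DIKI (by AKIN, RIFLE and an adjudication panel), produces ROC curves described as exploratory, and estimates sensitivity and specificity. Then: "BMs will be ranked according to their estimated probability of having a sensitivity and specificity of greater than 80" per cent. It does not say whether these estimates are apparent or corrected for having been tuned on the same patients.

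Protocol 9.1 plans "100 patients in the cisplatin cohort to have a minimum of 20 subjects" with AKI, plus 20 cancer controls and 20 healthy controls, and says that "20 cisplatin patients with AKI and 20 patients/subjects in each control cohort will enable an exploratory comparison between cohorts". Of the size itself it says: "The sample size of the cisplatin-treated and the control cohorts may be adjusted during the course of the study based on interim analyses".

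On the number of markers, section 7 states: "All biomarkers will be assessed in urine and Cystatin C and NGAL will additionally be assessed in plasma/serum". Its table of novel biomarkers has 23 urinary entries, or 22 without urinary creatinine itself.

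**The concern.** A cut-off picked because it separates cases from non-cases well in one sample will look better in that sample than in the next. Choosing between two expressions adds to this, and so does quoting the best of some twenty markers. The effect is largest where the numbers are smallest, which here is sensitivity, resting on the AKI cases.

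The marker list, the cut-offs and their apparent accuracy are what this study hands to the confirmatory stage. If confirmatory studies are sized on a sensitivity that is really much lower, or fix a cut-off on the strength of it, they start from a wrong premise.

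**Working it through.** **The plan's own figure.** 20 AKI cases in 100 is 20/100 = 20%. Section 9.1 gives no AKI rate, alpha, power or precision target, so there is no calculation to reproduce. If the true AKI rate is 20%, the binomial probability of at least 20 cases in 100 is 0.54; at 25% it is 0.90; at one-third it is 0.999, with about 33 expected. The one-third comes from 1.1 ("This occurs in about one-third of patient undergoing high dose cisplatin treatment") and refers to nephrotoxicity, not to AKI by AKIN or RIFLE.

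**Precision before any tuning.** Exact (Clopper-Pearson) 95% limits are 56% to 94% for 16/20 and 70% to 88% for 64/80.

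**Model for the optimism.** The documents give no true accuracies or correlations, so these are assumptions, shown as a range.
- Non-cases are N(0,1) and cases N(d,1). A marker with sensitivity = specificity = s at its best cut-off has d = 2Φ⁻¹(s).
- At a chosen cut-off c, true sensitivity is 1 − Φ(c − d) and true specificity is Φ(c). The Youden index is J = sensitivity + specificity − 1.
- For x correct out of n, the chance that the proportion exceeds 80% is taken from a Beta(x + 1, n − x + 1) distribution. The ranking probability is the product for sensitivity and specificity. The protocol does not give its formula; this is one natural reading.
- The cut-off is chosen and judged on the same 20 cases and 100 − 20 = 80 non-cases.

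**One marker, Youden cut-off.**
- True 75%/75%: apparent J 0.577, true J at the chosen cut-off 0.475, optimism 0.577 − 0.475 = 0.102.
- True 70%/70%: apparent 0.485, true 0.374, optimism 0.111.

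**Top-ranked of many, all truly 70%/70%, ranked on the probability above.**

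| Setting | Appears (sens/spec) | True at that cut-off | Gap in points |
|---|---|---|---|
| 22 independent markers, 20 vs 80 | 81/83 | 59/79 | 22 / 4 |
| 25 independent markers, 20 vs 80 | 82/84 | 59/79 | 23 / 5 |
| 25 independent markers, 33 vs 67 | 80/82 | 64/75 | 16 / 7 |

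With 25 markers and 20 cases, the estimated probability that both exceed 80% averages 0.36 for the top-ranked marker, against 0.05 for a single marker, although none qualifies.

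**Share of studies with at least one marker strictly above 80% on both.** All truly 70%/70%: about 30% to 33% with 22 independent markers, and 38% with 25. With 25 markers all truly 65% it is 5%; all truly 75%, 95%; pure noise, 0 in 2,000 runs.

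**What correction achieves.** For one marker at 75%/75%, bootstrap correction moved the mean J from 0.577 to 0.51, leaving 0.51 − 0.475 = 0.035 of the 0.102, so about two-thirds of the optimism was removed. Another run cut the bias from about 0.09 to 0.02.

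**What correction does not change.** With 22 markers of true accuracy 55% to 85% (60 runs), the rank correlation between apparent and corrected order was 0.99, and the same marker came top in 90% of runs. Correlation with the true order was 0.83 apparent and 0.81 corrected.

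**The case against.** The strongest reply is that resampling details normally sit in the SAP, which is not shown, and that 9.2.1 excludes no correction. That stands: silence on bootstrap or cross-validation is not an error. What remains is that the protocol itself fixes an 80% criterion and assigns cut-off and expression choice to the same data. Followed as written, that gives apparent figures.

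The work is also called exploratory, and markers and cut-offs go on to a confirmatory stage. That too stands, and lowers the severity. The confirmatory stage would reveal an inflated sensitivity, but only after it had been designed on it.

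Ranking on a probability rather than a point estimate does allow for small numbers. It does not allow for the search over cut-offs and markers, as the 0.36 against 0.05 shows.

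The simulated tuning is partly inferred. Section 9.2.1 names no cut-off rule and does not say that the better expression enters the ranking; 2.1 makes the expression choice for later studies.

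Four stronger readings are tempting, and the material does not support them:
- That the ranking puts the wrong markers first. All markers are measured in the same patients, the optimism is broadly shared, and correction hardly moves the order.
- That pure chance markers will be promoted. In the simulation noise never reached 80%/80%; what appears to pass is moderate markers of about 70% to 75%.
- That everything rests on 20 patients. Only sensitivity does. Twenty is a planned minimum that may change, and specificity has about 80 cisplatin patients, with up to 40 controls besides if used.
- That most studies of 70%/70% markers would show a pass. A share near 79% arises only if exactly 80% counts; the protocol says greater than 80%, which gives about 30%.

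**Conclusion.** The point holds for the reported accuracy, not for the order of the markers. With 20 AKI and 80 non-AKI patients, a data-chosen cut-off inflates the Youden index of a single moderate marker by about 0.10. The top-ranked of 22 markers that are all truly 70%/70% overstates sensitivity by roughly 22 points and specificity by about 4. More cases shrink the gap in sensitivity but do not remove it: at 33 cases, with 25 markers, it is still about 16 points.

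These sizes rest on equal-variance binormal markers of equal true accuracy. If a few markers are truly much better than the rest, the winner's gap is smaller. Correlation between markers lowers the share of studies with an apparent pass. In the other direction, the seven post-dose time-points and three DIKI definitions are not modelled, and searching over them would add optimism.

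This is a cheap improvement of low-to-moderate severity.

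**What to change.** Add to 9.2.1 that sensitivity, specificity and the probability of both exceeding 80% are optimism-corrected by bootstrap or cross-validation, with the choice of cut-off and of expression repeated within each resample; that apparent and corrected values are reported side by side; and that corrected values are used to plan the confirmatory studies. The resampling detail can go in the SAP.

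Correction marker by marker deals with cut-off and expression only. Where a figure is quoted specifically for the leading marker, the ranking step should be repeated within the resample as well.

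The cost is a little more analysis code and slightly less favourable reported accuracy. No patients, visits or samples are added.
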